### Participants

#### Recruitment and power calculations

Clinical in-patients aged 18–65 years with a current diagnosis of major depression (ICD-10) will be continuously recruited from the Psychiatric Services Solothurn, Psychiatric Clinics of the University of Basel, Psychiatric Clinic Wyss, Münchenbuchsee, and the Psychiatric Clinic Sonnenhalde, Riehen. In previous studies with non-depressed individuals, individually tailored physical activity promotion was associated with a moderate effect (*d* = 0.50) on the primary outcome (physical activity) [80, 81]. So far, only one study exists examining physical activity counselling among out-patients with depression, yielding an adjusted odds ratios of 2.27 across the 4-month, 8-month, and 12-month follow-up (corresponding *d* = 0.45). Conversely, a relatively small effect size (*d* = 0.28) was observed in a Cochrane review of intervention studies promoting physical activity among generally healthy people [92]. Similarly, remote interventions such as telephone-based, app-based, and Internet-based coaching versus a control group were associated with rather small effect sizes for change in physical activity (*d* = 0.20) [93]. Given these observations, we assume a small-to-moderate effect of our intervention on the primary outcome (*d* = 0.30). Accordingly, the optimal sample size to detect a significant effect at follow-up is 278 participants (two independent groups, one-tailed, α-error probability = 0.05, power = 0.80). With 20% expected dropouts from baseline to follow-up [94], the targeted sample size is *N* = 334 (IG, *n* = 167: PCG, *n* = 167). This means that every centre will recruit approximately 40 participants per year (*n* = 20 in the IG, *n* = 20 in the PCG). Dependent on the size of the clinics, this corresponds to a recruitment rate of 20–25% of the patients. Enrolment will be systematically monitored by the sponsor-investigator in order to recruit a sufficient number of participants within the planned timeframe.

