### Data collection and statistical analysis

Types of data to be collected include: quantitative data on social and demographic background, anthropometric measurements, physical activity, cardiorespiratory fitness, exercise-related variables (cognitive and social determinants), indicators of psychological functioning, cardiovascular risk factors, and biomarkers of MDD; and qualitative data, based on semi-structured interviews, on the acceptability and perceived usefulness of the intervention among the patients. The collected data will be entered and merged into a single datafile. Statistical analysis will be performed using SPSS.

Treatment group, age, gender, baseline HAMD17 score, and the amount of previous depressive episodes will be selected as covariables. Changes in outcome variables over the three time points will be analysed using repeated-measures analyses of covariance (rANCOVAs), with a between-subject factor group (IG vs PCG) and a within-subject factor time (baseline, post intervention, follow-up). If significant group or time interactions are present, Bonferroni-adjusted post-hoc tests will be performed to identify individual differences. The statistical significance level will be defined at α = 0.05. Effect sizes will be calculated according to the recommendations of Cohen [183], with 0.49 ≥ *d* ≥ 0.20 indicating small effect (e.g. negligible practical importance), 0.79 ≥ *d* ≥ 0.50 indicating medium effect (moderate practical importance), and *d* ≥ 0.80 indicating large effect (crucial practical importance).

In the case of missing values (e.g. when patients drop out before follow-up), all analyses will be performed with and without intention to treat [184]. After a thorough dropout analysis, a decision will be reached regarding the method best suited to analyse intention-to-treat effects (e.g. last observation carried forward, imputation of missing values) [185].

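### The sample size rests on a one-tailed comparison, but the planned rANCOVA F tests at α = 0.05 are non-directional; under the protocol's own two-group model, two-sided power at 278 is about 70%, not 80%

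*Protocol article*

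**What the plan says.** Under Recruitment and power calculations, the protocol article assumes d = 0.30 on the primary outcome and states that "the optimal sample size to detect a significant effect at follow-up is 278 participants". The conditions are given in brackets: "two independent groups, one-tailed, α-error probability" 0.05, with power 0.80. An allowance for 20% dropout then takes the target to 334, with 167 per arm.

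Under Data collection and statistical analysis, the test is different: "Changes in outcome variables over the three time points will be analysed using repeated-measures analyses of covariance (rANCOVAs"), with group (two arms) as the between-subject factor and time (baseline, post intervention, follow-up) as the within-subject factor. Bonferroni-adjusted post-hoc tests follow a significant result. On the level it says: "The statistical significance level will be defined at" α = 0.05. It does not mention a one-tailed test, and neither section gives a reason for a directional hypothesis.

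The abstract defines the primary outcome as accelerometer-measured physical activity at follow-up, 12 months after discharge.

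**The concern.** A power figure describes one particular test. Here the sizing test is one-tailed at 0.05, and the analysis consists of F tests at 0.05. A 1-df F test of group is equivalent to a two-sided t-test. The group-by-time test over three time points is a 2-df omnibus test, which has no direction at all. Neither matches a one-tailed comparison at follow-up.

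What is at stake is how a null result would be read. A reader would take it to come from a trial with a 20% chance of missing d = 0.30, and the article does not support that figure for a non-directional test. The margin is thin: the same paragraph cites effects of 0.20 for remote coaching and 0.28 for interventions in generally healthy people, both below the assumed 0.30.

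**Working it through.** **Inputs.** From the power paragraph: d = 0.30, α = 0.05, one-tailed, power 0.80, 278 evaluable (139 per arm), 20% dropout, target 334 (167 per arm). From the analysis section: rANCOVA, group (2) by time (3), α = 0.05.

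**Step 1: reproduce 278.** The article does not name the test, so a two-sample t-test is assumed. The noncentrality is d·√(n/2), with n per arm and 2n − 2 degrees of freedom. For n = 139 it is 0.30 × √69.5 = 2.50.
- One-sided 0.05: power 0.802 (normal approximation: Φ(2.50 − 1.645) = 0.804). 139 is the smallest n per arm that reaches 0.80, so the total is 278, an exact match.
- Two-sided sizing would have needed 176 per arm, or 352. Only the one-tailed calculation gives 278.

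**Step 2: change sidedness and nothing else.** Two-sided 0.05, power from the noncentral t:

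| Completers | Per arm | Two-sided power |
|---|---|---|
| 267 | about 133.5 | 0.685 |
| 278 | 139 | 0.703 |
| 334 (no loss) | 167 | 0.780 |
| 352 | 176 | 0.80 (smallest n that reaches it) |

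The effect of sidedness alone is the drop from 0.802 to 0.703 at 278.

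**Step 3: separate the dropout effect.** 278 × 1.20 = 333.6, which gives the target of 334. Losing 20% of 334 leaves 334 × 0.80 = 267, not 278. Ending with 278 would need 278/0.80 = 347.5, so 348. The 0.685 in the table therefore combines the sidedness mismatch with this separate shortfall.

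**Step 4: can the rANCOVA's own power be found?** Not from the article. As an illustration, assume SD 1, equal correlation ρ between visits, no baseline difference, a difference *a* at the post-intervention visit and 0.30 at follow-up, with 139 per arm. The noncentrality of the 2-df group-by-time F test is

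λ = (n/2) × (2a² + 2 × 0.30² − 2 × 0.30a) / [3(1 − ρ)].

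- ρ = 0.3, a = 0.15: λ = 69.5 × 0.135/2.1 = 4.47, power 0.455.
- ρ = 0.5, a = 0.15: λ = 69.5 × 0.135/1.5 = 6.26, power 0.601.
- ρ = 0.7, a = 0 or 0.30: λ = 69.5 × 0.18/0.9 = 13.9, power 0.925.

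Over ρ from 0.3 to 0.7 and a from 0 to 0.30, power runs from about 0.46 to 0.93. All of these inputs are assumptions.

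**Step 5: a baseline-adjusted 12-month contrast.** For a two-sided ANCOVA of follow-up activity on baseline activity, the effective d is 0.30/√(1 − r²), where r is the assumed baseline-to-follow-up correlation. With 267 completers:
- r = 0.3: effective d = 0.30/0.954 = 0.314, power 0.726.
- r = 0.5: effective d = 0.30/0.866 = 0.346, power 0.805.

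**The case against.** **The one-tailed assumption is disclosed.** This is true. Anyone who reads the power paragraph can see how 278 arose, and a one-tailed design can be legitimate. But the directional test then has to be the one analysed, and the analysis section does not carry it over. A fuller plan may exist, but the article states both the sizing and the analysis, and as stated they do not match.

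**70% is not the power of the planned analysis.** This stands. An unadjusted two-sided two-group comparison is not the rANCOVA either. A reader might infer that the trial's real power is 70%, or that it has a 30% chance of missing d = 0.30. The article does not support that, because the rANCOVA's power depends on correlations and a post-intervention effect that it does not give, and plausible inputs put it on either side of 80%. The 70% is the two-sided power of the protocol's own planning model.

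**Baseline adjustment would make up the difference.** Only in part, and only under an assumption. With 267 completers, r = 0.3 lifts power from 68.5% to 72.6%, about 4 of the 12 points lost against 80.2%. At r = 0.5 power reaches 80.5%. The covariables listed are treatment group, age, gender, baseline HAMD17 score and number of previous episodes; baseline activity enters as a level of the time factor. The article therefore does not describe this model.

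**Type I error is not affected.** Correct. An F test at α = 0.05 does not inflate false positives. The defect lies in the stated power.

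**Conclusion.** The mismatch is real. The 80% power is that of a one-tailed two-group comparison, while the stated analysis is non-directional at α = 0.05. Under the protocol's own two-group model with d = 0.30, testing two-sided lowers power at 278 completers from 80.2% to 70.3%, and 352 completers would be needed for 80%. These figures assume a two-sample t-test without covariate gain, and the first of them reproduces the article's sample size exactly.

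The finding goes no further than that. It does not establish the rANCOVA's power, and it does not show that the trial must enrol more patients. It should be fixed because a stated property of the primary comparison is unsupported. It does not threaten the validity of the test.

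**What to change.** In the power paragraph:
- Keep the statement that 278 came from a one-tailed calculation. It is the only basis that reproduces a sample size already in use, since recruitment began in January 2019.
- Add that the primary test is two-sided at α = 0.05.
- Restate power for the two-group comparison as about 70% at 278 completers and about 69% at the 267 left after 20% loss from 334, noting that the second figure also reflects the dropout inflation.

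Optionally, in the analysis section, name the primary contrast as a two-sided ANCOVA of 12-month accelerometer activity adjusted for baseline accelerometer activity. Quote its power with the correlation labelled as an assumption: about 73% at r = 0.3 to 81% at r = 0.5, with 267 completers. Do not claim that adjustment recovers most of the loss.

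The cost is a few sentences and a less favourable stated power. Patient numbers and trial conduct do not change.

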**Methods:**

The study is designed as a multi-centric two-arm randomized clinical trial including an intervention group and a placebo control group, allocation concealment, single-blinding, and intention-to-treat analysis. Participants (*N* = 334) will be continuously recruited from four clinics specialized in the treatment of MDD. The intervention builds on a standardized, theory-based, low-cost lifestyle physical activity counselling programme, which was specifically designed for an in-patient rehabilitation setting. The placebo control condition consists of general instructions about health-enhancing physical activity. Data assessments will take place 2–3 weeks after admission to in-patient treatment (baseline), and 6 weeks (post) and 12 months (follow-up) after discharge from in-patient treatment. The primary outcome is objectively assessed physical activity at follow-up.

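### The 20% dropout allowance is multiplied on rather than divided out, so N = 334 yields about 267 completers instead of the 278 required

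*Protocol article*

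**What the plan says.** The calculation is in the protocol article under Recruitment and power calculations. It assumes a standardised effect of "our intervention on the primary outcome (*d* = 0.30") and the test settings "two independent groups, one-tailed, α-error probability = 0.05, power = 0.80". From these it concludes that "the optimal sample size to detect a significant effect at follow-up is 278 participants". The next sentence makes the attrition allowance: "With 20% expected dropouts from baseline to follow-up [94], the targeted sample size is" N = 334, split as "IG, *n* = 167: PCG, *n* = 167". No inflation formula is shown.

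The Methods paragraph of the abstract repeats 334 as the number who "will be continuously recruited from four clinics specialized in the treatment of MDD". It also fixes the time point: "The primary outcome is objectively assessed physical activity at follow-up". Under Study design, allocation takes place after the baseline assessment, so 334 is the number randomised.

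**The concern.** The requirement of 278 applies at follow-up, and the 20% loss is counted from baseline. The enrolled number therefore has to satisfy N × (1 − 0.20) ≥ 278. Adding 20% of 278 to 278 does not achieve this, because the loss applies to the larger enrolled number and not to the completers. The stated target looks like the product of that shortcut.

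If so, the trial is planned to end with fewer analysable patients than its own calculation requires, at the time point where the primary outcome is assessed. The 278 has no slack to absorb this, since it is the smallest equal-arm sample that reaches 80% power under the stated settings.

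**Working it through.** **Inputs**, all from Recruitment and power calculations: d = 0.30; one-tailed α = 0.05; power 0.80; two equal independent groups; 278 required at follow-up; 20% dropout from baseline to follow-up; target 334 (167 per arm).

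**1. Reproduce the 278.** For n per arm, power is the probability that a noncentral t variable with 2n − 2 degrees of freedom and noncentrality d·√(n/2) exceeds the one-sided 5% critical value.

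- Solving for 80% power gives n = 138.07, so 139 per arm and 278 in total. This matches the protocol exactly.
- The normal approximation gives 276.
- The two-sided versions give 352 (t) and 350 (normal). Neither matches, so the one-tailed basis is confirmed.

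**2. Reproduce the 334.**

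| Rule | Total | Per arm |
|---|---|---|
| Multiply by 1 + 0.20 | 278 × 1.20 = 333.6 → 334 | 139 × 1.20 = 166.8 → 167 |
| Divide by 1 − 0.20 | 278 / 0.80 = 347.5 → 348 | 139 / 0.80 = 173.75 → 174 |

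Only multiplication returns the printed figures. The gap of 348 − 334 = 14 is too large to be rounding.

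**3. What 334 delivers at 20% dropout.**

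- Completers: 334 × 0.80 = 267.2, or 133.6 per arm.
- Shortfall: 278 − 267 = 11.
- Largest dropout that still leaves 278: 1 − 278/334 = 0.168, i.e. 16.8%.

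**4. Power at each completer number**, with d = 0.30 and α = 0.05.

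| Completers per arm | Noncentrality d·√(n/2) | One-tailed power | Two-sided power |
|---|---|---|---|
| 139 (required) | 0.30 × √69.5 = 2.50 | 80.2% | 70.3% |
| 133.6 (expected from 334) | 0.30 × √66.8 = 2.45 | 78.8% | 68.5% |

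The inflation error costs 80.2 − 78.8 = 1.4 points one-tailed and 70.3 − 68.5 = 1.8 points two-sided. The larger gap between the two power columns comes from the choice of a one-tailed test, which is a separate matter.

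**The case against.** The slip itself is not in dispute. The case on the other side is that it hardly matters.

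- **Size.** A loss of 1.4 points is small beside the uncertainty in d, which was chosen by judgement from values of 0.20, 0.28, 0.45 and 0.50. With 267 completers, 80% power is reached at about d = 0.305 instead of 0.30. This stands, and it limits how much weight the point can carry.
- **Covariate adjustment.** The power figures describe an unadjusted t-test, while the Data collection and statistical analysis section plans repeated-measures ANCOVA with covariates. As an assumption (the documents give no figure), covariates explaining about 4% of outcome variance would offset the loss, since 267.2/278 = 0.96; explaining none would leave power at 78.8%. This is a fair caution about actual power, but the sample-size statement claims no such gain and the inflation remains wrong.
- **Recruitment plan.** Correcting N barely changes the site workload. Per centre, 334/4 = 83.5 and 348/4 = 87; at 40 a year these take 2.09 and 2.18 years. Both are compatible with an approximate rate of 40, so the error does not distort the per-centre plan in practice.
- **No stated completer count.** The protocol never prints 267, so that number is derived. It does print the 278 needed at follow-up, and 334 with 20% loss does not supply it.
- **Two-sided figures.** Most of the distance from 80% to 68.5% is due to sidedness. Those figures are for reference only and should not be read as the cost of this error.

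None of this makes 334 consistent with 278 and 20%. Reading the 20% as a fraction of completers would reproduce 334, but it conflicts with a dropout rate counted from baseline.

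**Conclusion.** The concern holds. The stated requirement (278 at follow-up), dropout (20% from baseline) and target (334) are mutually inconsistent, and 334 comes from multiplying by 1.20 where division by 0.80 was needed. At 20% dropout the plan is short by 11 completers, equivalent to 14 enrolled patients, and one-tailed power is 78.8%, just under the stated 80%.

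The conclusion assumes that the 20% covers all loss from the primary analysis. The Objective physical activity section also excludes participants without at least 5 valid accelerometer days. If those exclusions come on top of the 20%, the shortfall is larger; the protocol gives no rate, so this cannot be sized.

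The practical effect is small and does not undermine the design. The figure should still be corrected, because it is wrong as written, it is the headline sample size, and the correction costs next to nothing.

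**What to change.** Either of two corrections resolves it.

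1. **Keep N = 334 and correct the sentence.** State that 20% dropout leaves about 267 participants at follow-up, giving about 79% power on the one-tailed test, or state that 334 allows for 16.8% dropout. If a two-sided test is also reported, the corresponding power is 68–69%. The cost is one sentence, with no change to recruitment.
2. **Correct the target to 348 (174 per arm)**, in both the power section and the abstract. The cost is 14 more patients, or 3.5 per centre on average.

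The first is sufficient and proportionate, particularly as recruitment has already started. Whichever is chosen, show the inflation as required N divided by (1 − dropout), and say whether the 20% includes participants without valid accelerometer data.

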#### Screening

A structured clinical interview will be conducted by a psychiatrist to ensure that all participants fulfil the ICD-10 diagnosis for a single episode (F32), recurrent MDD (F33), or bipolar disorder type II (F31-II). The screening also includes assessment of the duration of the current depressive episode, the number of previous depressive episodes, psychiatric and somatic comorbidities, and family history of psychiatric and somatic conditions. To assess symptom severity, a trained staff member will apply the 17-item Hamilton Depression Rating Scale (HAMD17) [95] as part of a clinical interview [96], while patients’ self-ratings are based on the 21-item Beck Depression Inventory (BDI) [97, 98], along with the short version of the International Physical Activity Questionnaire (IPAQ) [99] to assess self-reported physical activity (referring to the last week before entering the clinic).

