### Procedures

#### Data assessment

Screening will take place in the first week after admission to in-patient treatment. Identical data assessment will take place 2–3 weeks after admission to in-patient treatment (baseline), and 6 weeks (post) and 12 months (follow-up) after discharge from in-patient treatment. The primary outcome is objectively assessed physical activity (Actigraph wGT3x-BT monitor, 7 days). Secondary outcomes are self-reported physical activity, cardiorespiratory fitness, autonomic function cognitive and social determinants of exercise, depression severity, self-perceived physical and psychological health, insomnia symptoms, cognitive function, cardiovascular health risk markers, and biomarkers of MDD. Moreover, the serotonin transporter (5-HTT) polymorphic promoter region (5-HTTLPR) is assessed as a potential moderator of intervention effects [21]. More information regarding the various instruments is presented in the following.

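### Pre-admission activity (IPAQ), held for every patient from screening, is left out of the covariates, so some precision on follow-up activity may be lost

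*Protocol article*

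**What the plan says.** All places are in the protocol article.

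- **Screening:** the short IPAQ records self-reported activity, "referring to the last week before entering the clinic". Under Criteria for inclusion/exclusion, patients must score below 150 min/week of moderate-to-vigorous activity, so everyone randomised has a value.
- **Data assessment:** "Identical data assessment will take place 2–3 weeks after admission to in-patient treatment (baseline"). The intervention section puts the average in-patient stay at 6 to 8 weeks, so this accelerometer week normally falls on the ward. The follow-up measurement comes 12 months after discharge.
- **Data collection and statistical analysis:** "Treatment group, age, gender, baseline HAMD17 score, and the amount of previous depressive episodes will be selected as covariables". The model is a repeated-measures ANCOVA with group as between-subject factor and time (three occasions) as within-subject factor. Baseline activity is therefore the first level of time, not a covariate.
- **Covariates:** the list of potential covariates is demographic and clinical. IPAQ is not on it.

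**The concern.** The outcome of interest is activity in ordinary life a year after discharge. The accelerometer baseline describes a patient in hospital, with a routine set by the clinic and exercise offers open to both arms. The IPAQ answer is the one earlier value that refers to the patient's own surroundings, yet the plan uses it only to decide eligibility.

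Adjusting for a prognostic variable measured before randomisation reduces residual variance and introduces no bias. If IPAQ carries information about later activity that the ward week does not, leaving it out gives up precision that would cost almost nothing to keep. What is at stake is efficiency only, not the validity of the comparison.

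**Working it through.** **1. The plan's own figure.** Under Recruitment and power calculations: "we assume a small-to-moderate effect of our intervention on the primary outcome (*d* = 0.30"), with "two independent groups, one-tailed, α-error probability = 0.05, power = 0.80". For a two-sample t test with n per arm, the noncentrality is d·√(n/2) on 2n − 2 degrees of freedom. The smallest n giving 80% one-tailed power is 139 per arm, or 278 in total, at a power of 80.2%. This matches "the optimal sample size to detect a significant effect at follow-up is 278 participants".

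**2. Evaluable patients.** "With 20% expected dropouts from baseline to follow-up", "the targeted sample size is *N* = 334 (IG, *n* = 167: PCG, *n* = 167"). Then 334 × 0.8 = 267.2, about 267. Without IPAQ, power at d = 0.30 is 78.8% one-tailed and 68.5% two-sided.

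**3. Effect of one more covariate.** Let r be the partial correlation of IPAQ with the analysed outcome, given the other model terms. Residual variance is multiplied by 1 − r², so d becomes 0.30/√(1 − r²). The documents give no value for r; the range 0 to 0.3 is an assumption.

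| Assumed partial r | Variance removed | Power at 267, one-tailed | Power at 267, two-sided |
|---|---|---|---|
| 0 | 0% | 78.8% | 68.5% |
| 0.1 | 1% | 79.2% | 69.0% |
| 0.2 | 4% | 80.3% | 70.3% |
| 0.3 | 9% | 82.1% | 72.6% |

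**4. Range restriction.** Entry requires IPAQ below 150 min/week, which narrows the covariate and weakens any correlation. The share of patients below the cut is not given. In a simulated bivariate normal cut at the 30th, 50th and 70th percentile of the covariate, an unrestricted correlation of 0.30 falls to 0.16, 0.19 and 0.22. Squared, that is about 3% to 5% of variance. An unrestricted 0.50 would be needed to leave 0.29 to 0.38. These are marginal correlations; allowing for the other model terms changes them further. About 0–4% is therefore the more likely range.

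**5. The planned contrast.** Let Y be follow-up activity, B the ward baseline and I the IPAQ. In the group-by-time comparison of baseline with follow-up, IPAQ helps only through its correlation with change:

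r = (r_YI − r_BI) / √(2 − 2·r_YB)

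Illustrations, all assumed:
- r_YI = r_BI: r = 0, no gain.
- r_YI = 0.2, r_BI = 0.1, r_YB = 0.4: 0.1/√1.2 = 0.091, or 0.8% of variance.
- r_YI = 0.2, r_BI = 0, r_YB = 0.2: 0.2/√1.6 = 0.158, or 2.5%.
- r_YI = 0.3, r_BI = 0, r_YB = 0.4: 0.3/√1.2 = 0.274, or 7.5%.

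The gain depends on IPAQ tracking follow-up activity more closely than it tracks the ward week. That is plausible, since the pre-admission and follow-up weeks are both spent outside the clinic, but the article does not show it.

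**The case against.** The strongest reply is that nothing here is an error. Omitting an optional covariate biases nothing, contradicts nothing and leaves every stated number intact, and a separate analysis plan might add it. That stands, with one qualification: the article gives a definite covariable list rather than leaving the choice open, so it is fair to comment on what that list omits.

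The prognostic value is also unproven. IPAQ is one self-reported week, shortly before a psychiatric admission and truncated by the entry rule. The only correlation between self-report and accelerometer in the article (0.30–0.70) is for SIMPAQ in university students. That is another instrument in another population and says nothing about prediction over a year. This stands too, and is why the range starts at zero.

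Three stronger readings are tempting, and the documents support none of them:
- **That precision is certainly being lost.** This needs a non-zero partial correlation, which the article does not give.
- **That IPAQ would make good the gap between 267 and 278.** At r = 0.20, 267/(1 − 0.04) is about 278, but this is a coincidence at one chosen value of an unknown. The gap itself comes from inflating 278 by 1.2 instead of dividing by 0.8 (which gives 348). That is a separate sample-size matter with its own remedy.
- **That the power table describes the planned model.** It scales a two-group t test; in the group-by-time contrast the gain can be nil.

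**Conclusion.** The point holds as an optional improvement of low severity. The plan records a pre-randomisation measure of activity outside the clinic for every patient and does not adjust for it, while its only other baseline activity value is normally a ward week. The possible gain is 0–9% of residual variance for an assumed partial correlation of 0 to 0.3, and more likely 0–4%. At 267 evaluable patients and d = 0.30 that is at most 3.3 percentage points of one-tailed power (82.1 − 78.8). The size rests wholly on an assumed correlation, and it vanishes in the group-by-time contrast if IPAQ relates equally to ward and follow-up activity.

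**What to change.** In Data collection and statistical analysis, add screening IPAQ moderate-to-vigorous minutes per week, as a continuous variable, to the covariables for the accelerometer outcome and for SIMPAQ. Baseline accelerometry can stay as a level of the time factor; the addition does not replace it. State the choice before any outcome data are analysed, since adding the variable later would look data-driven. The cost is one line of text and about one degree of freedom per contrast, with no new data and no extra visit.
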